# Comparison of the pathological response to 2 or 4 cycles of neoadjuvant CAPOX in II/III rectal cancer patients with low/intermediate risks: study protocol for a prospective, non-inferior, randomized control trial (COPEC trial)

**DOI:** 10.1186/s13063-023-07405-x

**Published:** 2023-06-13

**Keywords:** Rectal cancer, Neoadjuvant chemotherapy, Pathological tumor regression grade, CAPOX

## Abstract

**Background:**

For patients with low- and intermediate-risk stage II/III rectal cancer, current studies have reached a consensus that preoperative radiotherapy may be dispensed with, and neoadjuvant chemotherapy (NCT) alone might achieve an accepted local control. Our previous phase II study has evidenced that the morphological response of NCT could be better judged at a relatively early stage. Low- and intermediate-risk stage II/III rectal cancer patients could achieve a high rate of tumor shrinkage and downgrade after only 4 cycles of NCT and obvious tumor morphological changes could be observed after 2 cycles of NCT. However, there is still a lack of more detailed stratification and evidence for pathological criteria. The aim of the present study (comparison of the pathological response to 2 or 4 cycles of neoadjuvant CAPOX in II/III rectal cancer patients with low/intermediate risks, COPEC trial) is to determine the pathological tumor regression grade (pTRG) rate of 2 or 4 cycles of NCT in low- and intermediate-risk stage II/III rectal cancer and verify the feasibility of early identification of chemotherapy-insensitive population.

**Methods/design:**

This is a multicenter, prospective, non-inferior, randomized controlled trial (RCT) initiated by West China Hospital of Sichuan University and designed to be conducted in fourteen hospitals around China. Eligible patients will be centrally randomized into 2 or 4 cycles of CAPOX in a 1:1 ratio using the central automated randomization system offered by the O-trial online system (https://plus.o-trial.com/) and accept total mesorectal excision after 2 or 4 cycles of CAPOX (oxaliplatin 130 mg/m^2^, once daily on day 1, every 21 days and capecitabine 1000 mg/m^2^, twice daily on days 1 to 14, every 21 days). The primary endpoint is the proportion of patients with pathological no-tumor regression (pTRG 3), which is determined postoperatively by each sub-center and verified by the primary center.

**Discussion:**

COPEC trial is designed to verify that the preoperative CAPOX chemotherapy for low- and intermediate-risk stage II/III rectal cancer could achieve a good response judgment after 2 cycles and obtain the tumor pathological response rate after 2 cycles of CAPOX. We hope the COPEC trial could help in establishing a consensus standard of low- and intermediate-risk rectal cancer and the early identification of stage II/III rectal patients with low- and intermediate-risk who are poorly responding to NCT.

**Trial registration:**

Clinicaltrial.gov NCT04922853. Registered on June 4, 2021.

**Supplementary Information:**

The online version contains supplementary material available at 10.1186/s13063-023-07405-x.

## Background

Neoadjuvant chemoradiotherapy (NCRT) has progressively been accepted as a preoperative treatment for advanced rectal cancer. Many previous large randomized controlled trials (RCTs) [1–4] have shown that NCRT can effectively reduce the local recurrence rate after surgery. NCRT has been recommended as a priority standard treatment for stage II/III rectal cancer by National Comprehensive Cancer Network (NCCN) guidelines [5].

However, despite reducing the local recurrence rate, NCRT has not been proven with improved overall survival and may also bring radio-related adverse effects [4]. Indeed, the introduction of total mesorectal excision (TME) technique, characterized by using sharp dissection along the mesorectal fascia, has reduced the local recurrence rates as low as 5–15% [6, 7]. Local recurrence is no longer the main factor leading to tumor recurrence and death after radical resection. Our previous prospective stratified randomized controlled study [8] divided stage II/III rectal cancer into high-risk and intermediate-low-risk groups according to 5 dimensions (external invasion > 5 mm, lymph node > 8 mm, mesorectal fascia (MRF) ( +), low anterior wall T3, peripheral growth). Both groups were further randomly assigned to the radiotherapy group (receiving short-course radiotherapy with immediate TME surgery) and the surgery group (receiving upfront TME surgery alone). The study showed that the local recurrence rate of rectal cancer in the intermediate-low risk group (whether received radiotherapy or not) was extremely low, with a 3-year cumulative local recurrence rate of 3% [8], indicating that at least part of patients with intermediate-low risk was less likely to benefit from radiotherapy, which was also similar to other studies [9–15]. At the same time, radiotherapy did not bring a significant 5-year survival benefit in either group.

Although current studies suggest that patients with low- and intermediate-risk stage II/III rectal cancer could consider dispensing with preoperative radiotherapy, and NCT alone might achieve an accepted local control, there is still a lack of more detailed stratification and evidence for pathological criteria. For this reason, we have conducted a phase II study that included low- and intermediate-risk stage II/III rectal cancer for NCT alone and found that the proportion of patients with tumor shrinkage and downgrade after only 4 cycles of chemotherapy for low- and intermediate-risk stage II/III rectal cancer was 78.7%, with the pCR rate of 21.3% [16]. We also found that the 4 cycles of CAPOX were effective, and obvious tumor morphological changes were observed after 2 cycles (duration 6 weeks), with a predicted AUC value of 0.862 (0.751, 0.973). These findings suggested that the morphological response of NCT could be better judged at a relatively early stage. Therefore, we tended to hold the view that a considerable number of patients would be able to achieve tumor regression, and the pathological effect would reach tumor regression grade (TRG) 2 or better results after two cycles of NCT.

Currently, there is still no reliable preoperative method of assessing tumor response after NCT [17, 18]. Based on our previous phase II study, to verify that the CAPOX chemotherapy for low- and intermediate-risk stage II/III rectal cancer could achieve a good response judgment after 2 cycles, and obtain the tumor pathological response rate in the early 2 cycles, we intend to conduct a prospective, non-inferior, randomized, controlled study (COPEC trial) to determine the pathological tumor regression grade (pTRG) rate of 2 or 4 cycles of NCT in low- and intermediate-risk stage II/III rectal cancer and explicit the feasibility of early identification of chemotherapy-insensitive population.

## Methods/design

### Objective

The primary objective of this study is to prospectively evaluate that the pathological response rate after 2 cycles of CAPOX is not inferior to that of 4 cycles in patients with low-risk and intermediate-risk stage II/III rectal cancer, which may provide evidence for the feasibility of early identification of chemotherapy-insensitive population.

The secondary objectives are as follows: (1) to explore the difference in clinical remission rate between 2 and 4 cycles of CAPOX in patients with low-risk and intermediate-risk stage II/III rectal cancer; (2) to explore the effectiveness/ineffectiveness of NCT at early cycles (after 2 cycles of CAPOX) in predicting the long-term prognosis (3 years overall survival (OS)/disease-free survival (DFS)); (3) to confirm the perioperative safety of NCT alone; (4) to construct a model using 2-cycle imaging indicator to predict a 4-cycle pathological remission; and (5) to explore the feasibility of artificial intelligence (AI)-assisted imaging indicators to predict pTRG after NCT.

### Patients and study design

This is a multicenter, prospective, non-inferior, randomized controlled study initiated by West China Hospital of Sichuan University and designed to be conducted in fourteen hospitals around China (Additional file 1).

Patients with low-risk and intermediate-risk stage II/III rectal cancer are designed to be included in the study. The flow diagram has been shown in Fig. 1. In brief, patients diagnosed with rectal cancer will be evaluated by enhanced abdominal CT, pelvic MRI, and transrectal ultrasonography (TRUS) and staged according to the European Society for Medical Oncology (ESMO) guidelines [19]. Eligible patients will be randomized to accept 2 or 4 cycles of pre-preoperative CAPOX. Re-evaluation will be performed after 2 cycles of CAPOX (2 and 4 cycles group) and 4 cycles of CAPOX (4 cycles group). MrTRG will be recorded and verified by pTRG after TME surgery. Detailed criteria for mrTRG and pTRG have been listed in Additional files 2 and 3, respectively.

**Fig. 1 Fig1:**
[figure not shown]
Flow diagram

Low- and intermediate-risk stage II/III rectal cancer was defined as (1) middle and low rectal cancer (below the peritoneal reflection): T3a-bN0-1M0, EMVI ( ±), MRF (-) (≥ 2 mm) and middle and high rectal cancer (above the peritoneal reflection): T3a-c/T4aN0-1M0, EMVI ( ±), MRF (-) (≥ 2 mm); (2) mesorectal lymph node with short diameter ≥ 8 mm or highly suspected metastasis not more than 3; and (3) the short diameter of the lateral lymph node ≤ 7 mm. Inclusion, exclusion, and withdrawal criteria have been detailed in Table 1. The screening process is set to be performed by experienced surgeons at each center. Enrolled patients are allowed to quit at any time without any reason or responsibility.

**Table 1 Tab1:** Details of the inclusion, exclusion, and withdrawal criteria

Inclusion criteria	
1)	Patients aged between 18 and 75 of either sex
2)	Patients with low- and intermediate-risk stage II/III rectal cancer evaluated by MRI and TRUS: middle and low rectal cancer (below the peritoneal reflex line): T3a-bN0-1M0, EMVI ( ±), MRF (-) (≥ 2 mm) and middle and high rectal cancer (above the peritoneal turning line): T3a-c/T4aN0-1M0, EMVI ( ±), MRF (-) (≥ 2 mm) Mesangial lymph node with short diameter ≥ 8 mm or highly suspected metastasis no more than 3 The short diameter of the lateral lymph node ≤ 7 mm Patients with ultra-low rectal cancer who match the above criteria and can achieve negative circumferential resection margin under extralevator abdominoperineal excision (ELAPE) surgery will be included in the group
3)	In colonoscopy or anal examination, the lower boundary of the lesion is ≤ 12 cm from the anal verge
4)	Patients with no distant metastasis (including suspected lung nodule metastasis) confirmed by chest and abdomen CT examination; no extra-regional lymph node metastasis (≥ 10 mm)
5)	Pathologically diagnosed rectal adenocarcinoma
6)	Eastern Cooperative Oncology Group (ECOG) score: 0–1
7)	Patients with primary rectal cancer who have not received surgery (except palliative ostomy), radiotherapy, systemic chemotherapy, or other anti-tumor treatments before enrollment
8)	The main organ function is normal and meets the following standards: (1) blood routine criteria: HB ≥ 9 g/dL, WBC ≥ 3.5/4.0 × 10^9^/L, neutrophil ≥ 1.5 × 10^9^/L, PLT ≥ 100 × 10^9^/L; (2) blood biochemical criteria: Crea and BIL ≤ 1.0 times the upper limit of normal value (ULN), ALT and AST ≤ 2.5 times the upper limit of normal value (ULN), alkaline phosphatase (ALP) ≤ 2.5 × UNL, total bilirubin (Tbil) ≤ 1.5 × UNL
9)	No history of 5-Fu and platinum drug allergy
10)	Females of childbearing age must undergo a pregnancy test (serum or urine) 7 days before enrollment with a negative result and are willing to use appropriate contraceptive methods during the trial and 8 weeks after the last administration
11)	Patients voluntarily join the study and sign informed consent forms with good compliance and follow-up
Exclusion criteria joined	
1)	Patients considering lynch syndrome
2)	Patients who do not consider metastasis in the initial diagnosis but proved to be distant metastases during the treatment
3)	Previously or concurrently suffering from other malignant tumors (including concurrent colon cancer), except for cured skin basal cell carcinoma and cervical carcinoma in situ
4)	Pregnant or nursing women
5)	Lateral lymph nodes ≥ 7 mm
6)	Patients with severe cardiovascular disease and diabetes difficult to control
7)	Patients with mental disorders
8)	Patients with severe infection
9)	Patients undergoing thrombolysis/anticoagulation therapy with bleeding diathesis or coagulation dysfunction, or suffering aneurysm, stroke, transient ischemic attack in the past year
10)	Patients with a history of kidney disease, urinary protein, or clinically abnormal renal function
11)	Patients with a history of gastrointestinal fistula, perforation, bleeding, or severe ulcer
12)	Patients with severe gastrointestinal diseases that affect the absorption of oral chemotherapy drugs
13)	Patients participating in another clinical trial within 4 weeks before treatment
14)	Patients pathologically diagnosed with mucinous component or the signet-ring cell carcinoma
Withdrawal criteria	
1)	Patients refusing further treatment
2)	Patients having severe adverse reactions to chemotherapy and being unable to complete 2 cycles of chemotherapy

### Randomization and intervention

Each sub-center will be responsible for potential enrollment and consent-taking. Central randomization will be performed as soon as the enrollment is determined using the central automated randomization system offered by the O-trial online system (https://plus.o-trial.com/). Sub-center will upload the information of eligible patients on the O-trial system, which will sequentially number and randomize the uploaded patients into 2 or 4 cycles of CAPOX in a 1:1 ratio automatically. No stratification is included in the current study.

Patents in both groups will undergo TME surgery after 2 or 4 of CAPOX. Each cycle of CAPOX includes oxaliplatin 130 mg/m^2^, once daily on day 1, every 21 days and capecitabine 1000 mg/m^2^, twice daily on days 1 to 14, every 21 days. TME surgery was performed by experienced colorectal surgeons 2–3 weeks after the last cycle of preoperative CAPOX.

Postoperative adjuvant treatment will be performed according to the ESMO and Chinese guidelines for colorectal cancer [19, 20]. Based on the pathological stage, patients with a positive CRM or N2 stage would be recommended to undergo postoperative radiotherapy. Adjuvant chemotherapy was recommended for N + patients. The long-term survival of the patients will be followed up.

### Data collection

Clinical, imaging, and follow-up data will be collected prospectively in the case report forms (Additional file 4) and reserved in the O-trial online database (https://plus.o-trial.com/), which is daily maintained by [name] and [name]. The O-trial online database is a secure, password-protected database and can be only accessible to authorized project staff.

Details of the evaluation items and time points have been shown in Table 2. During CAPOX, blood routine and biochemistry will be examined weekly to detect potential hematopoietic inhibition or liver or kidney function impairment. Tumor markers, at least including CEA and CA19-9, will be recorded every cycle. Imagological examination, including chest CT, abdominal enhanced CT, rectal MRI, and TRUS will be re-evaluated every 2 cycles.

**Table 2 Tab2:** Details of the evaluation items and time points

	Screening	After 2 cycles of CAPOX (4 cycles)	Preoperative evaluation	Intraoperative evaluation	Postoperative evaluation	Follow-up visit
Colonoscopy	×					
Chest CT	×	×	×			×
Abdominopelvic enhanced CT	×	×	×			×
Pelvic MRI	×	×	×			
TRUS	×	×	×			
Blood routine	×	×	×			×
Blood biochemical indicators	×	×	×			×
Tumor markers^a^	×	×	×			×
Intraoperative complications				×		
Blood loss				×		
Operation time				×		
Surgical approach				×		
Perioperative complications					×	
Patient recovery					×	
Hospitalization time					×	
pTRG					×	

*TRUS* Transrectal ultrasonography, *pTRG* Pathological tumor regression grade

^a^At least includes CEA and CA19-9

Surgical information including tumor location and involvement, intraoperative stages, lymph node metastasis, operation times, intraoperative time, and complications will be recorded in detail in the surgical records. Perioperative complications are stratified by the Clavien-Dindo system. Resected rectal specimens will be fixed on a foam plate and sent to pathologists to determine the circumferential resection margin (CRM) and pTRG).

Follow-up is set throughout the whole trial (Additional file 5). In the preoperative CAPOX process, included patients will be asked to finish a series of questionnaires about quality of life (QOL) and tumor or NCT-related symptoms each cycle. Postoperative follow-up is set at 3 months after surgery, every 6 months in the first 5 years, and every year in subsequent years. QOL, blood tests, and CT imaging are also included in each follow-up. Adverse effects of postoperative adjuvant chemotherapy will also be recorded.

QOL is measured based on EORTC QLQ-C30 [21, 22], the EORTC QLQ-CR29 questionnaire [23], the International Prostatic Symptom Score (I-PSS) [24], and the sexual function evaluation questionnaire, which will be gathered by physician visits, mail, or WeChat and recorded in the online system for further analysis. Radiological examinations will be individually assessed by two radiologists blinded to the groups. Tumor imaging data, such as tumor long diameter, tumor volume, ADC value, and DWI value, will be collected and mrTRG will be determined accordingly. When a discrepancy arose, the imaging scans will be reviewed by two experienced radiologists in West China Hospital to reach a consensus. Based on MRI imaging, tumor response to NCT is classified into grades 1–5 (complete, good, moderate, slight and no response), and mrTRG4 and mrTRG5 represent a poor response to NCT. Criteria of the mrTRG have been listed in Additional file 2. Pathology examinations are performed by each sub-center and verified by the primary center to determine the pTRG (0–3). A pTRG3 represents poor tumor response to NCT. Specific standards of pTRG have been shown in Additional file 3.

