### Endpoints

The primary endpoint is the proportion of patients with pTRG3, which is determined postoperatively by each sub-center and verified by the primary center.

The secondary endpoints include (1) the proportion of patients with TRG on MRI (mrTRG) (1–5) after 2 cycles/4 cycles of CAPOX; (2) the proportion of patients with pTRG (0–2); (3) survival prognosis of patients with different pTRG, containing disease-free survival (DFS), local recurrence rate (LR), distant recurrence rate (DR), and overall survival (OS); (4) 3-year DFS and OS of patients with different pTRG; (5) the predicted imaging indicators of pTRG; (6) the accuracy of pTRG judged by imaging; (7) the adverse effects of chemotherapy; (8) the incidence of perioperative complications; and (9) the QOL of patients during chemotherapy and after surgery.

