### Data-analysis

The trial statistician, who will be blinded to randomization, will carry out the data analysis process. Before analysis, they will assess the integrity of collected data, and repeated or missing data will be described accordingly. Demographics and repeatedly measured clinical characteristics of participants will be summarized as the baseline.

SPSS for Windows, version 25 (IBM Corp, Armonk, NY), and GraphPad Prism for Windows, version 8.0.0 (GraphPad Software, San Diego, California), are used for data analysis. Continuous data are shown as the mean and standard deviation. Categorical variables are represented as percentages. Continuous variables are compared using the Mann–Whitney *U* test. Categorical variables are compared between groups using Fisher’s exact test or the chi-square test. Fisher’s exact test or the chi-square test is used to compare the proportions of patients with pTRG3, the proportion of patients with TRG on MRI (mrTRG) (1–5) after 2 cycles/4 cycles of CAPOX, and the proportion of patients with pTRG (0–2). Survival of patients (OS, DFS) is compared using Kaplan–Meier analysis. Statistical significance is defined as a *p*-value less than 0.05. Especially, in the 4 cycles of the CAPOX group, patients who receive less than 3 cycles of chemotherapy due to adverse effects or drop-out will be analyzed as the 2 cycles of the CAPOX group; others will be analyzed in the 4 cycles of the CAPOX group analysis.

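### The primary endpoint pTRG3 is graded locally and verified centrally with no masking, independent re-read or disagreement rule stated, although the secondary imaging endpoint has all the equivalents

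*Protocol article*

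**What the plan says.** The Endpoints section defines the primary endpoint and its reading in one sentence: "The primary endpoint is the proportion of patients with pTRG3, which is determined postoperatively by each sub-center and verified by the primary center". The Data collection section repeats the arrangement: "Pathology examinations are performed by each sub-center and verified by the primary center to determine the pTRG (0–3". The Abstract says the same. The grading criteria are placed elsewhere: "Specific standards of pTRG have been shown in Additional file 3". That file is not among the documents at hand.

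The Data collection section treats the imaging grade (mrTRG, a secondary endpoint) differently: "Radiological examinations will be individually assessed by two radiologists blinded to the groups". It also gives a rule for disagreement: "When a discrepancy arose, the imaging scans will be reviewed by two experienced radiologists in West China Hospital to reach a consensus". The Data-analysis section states one further layer of blinding: "The trial statistician, who will be blinded to randomization, will carry out the data analysis process".

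Three other facts bear on the point. Fourteen hospitals take part (Patients and study design). The arms differ in the number of chemotherapy cycles given before surgery (Randomization and intervention). Resected specimens are to be stored for pathological review (Ethics and safety).

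**The concern.** The primary result depends on one cut on an ordinal visual scale: pTRG3 against pTRG0–2. The center that gave two or four cycles necessarily knows the arm, and the local grade comes from that center. The initiating center then verifies it, but the article does not define what verifying involves. The article describes blinding for the radiologists and the statistician, yet says nothing about it for the assessment that produces the primary result.

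Two kinds of error are at stake.

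- **Error linked to knowledge of arm.** This acts directly on the between-arm difference. A reader who believes two cycles are enough may round down. A reader who doubts it may round up. The article contains both attitudes: the Background expects a considerable number of patients to reach grade 2 or better after two cycles, and the Discussion reports worry that two cycles may be too weak.
- **Error unrelated to arm.** This shrinks the difference. In a non-inferiority comparison, shrinkage favors the claim.

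The effect extends past the primary endpoint. pTRG defines or feeds several secondary endpoints and is the reference against which mrTRG is checked.

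**Working it through.** **Inputs from the Sample size calculation section.** The pTRG3 rate after 4 cycles is 27.9%. The increase after 2 cycles is expected to be no more than 10%. α is 0.05 with sidedness not stated, and power is 0.80. The margin δ is given as 0.05 and labelled a hazard ratio. The sample size is 249 per group, or 277 after 10% dropout.

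**Step 1: reproduce the plan's figure.** With p = 0.279 in both arms and margin m as a risk difference,

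n = 2p(1−p)(z₀.₉₅ + z₀.₈₀)² / m² = 2 × 0.279 × 0.721 × (1.645 + 0.842)² / 0.10² ≈ 248.7, so 249.

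249 / 0.9 = 276.7, so 277. Both stated figures are reproduced. A margin of 0.05 as a risk difference would need 995 per group (one-sided 5%), and a 10-point margin at one-sided 2.5% would need 316. The design behind 249 is therefore a 10-point margin at one-sided 5%. This is inferred from the arithmetic and is not what the article states as δ.

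**Step 2: chance of declaring non-inferiority.** With observed rates q₄ and q₂ and 249 per arm,

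P = Φ[(0.10 − (q₂ − q₄)) / SE − 1.645], where SE = √[(q₄(1−q₄) + q₂(1−q₂)) / 249].

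With perfect grading, a true 27.9% v 37.9% gives 5.0%, and true equality at 27.9% gives 80.0%.

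**Step 3: error linked to arm, 2-cycle arm only.** The error rates are assumptions.

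- Lenient: a share k of true pTRG3 is graded lower, so q₂ = 0.379(1−k).
- Harsh: a share k of true pTRG0–2 is graded 3, so q₂ = 0.379 + 0.621k. At true equality, q₂ = 0.279 + 0.721k.

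| Scenario | Observed difference at a true 10 points | False non-inferiority | Power at true equality |
|---|---|---|---|
| None | 10.0 points | 5.0% | 80% |
| Lenient, k = 5% | 8.1 points | 11.7% | 89% |
| Lenient, k = 10% | 6.2 points | 23.3% | 94% |
| Harsh, k = 5% | 13.1 points | 0.9% | 47% |
| Harsh, k = 10% | 16.2 points | 0.1% | 17% |

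Worked line for lenient 5%: q₂ = 0.379 × 0.95 = 0.360; SE = √[(0.2012 + 0.2304) / 249] = 0.0416; (0.10 − 0.081) / 0.0416 − 1.645 ≈ −1.19; Φ = 11.7%.

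**Step 4: error unrelated to arm.** With sensitivity Se and specificity Sp for pTRG3, the observed rate is Se·p + (1−Sp)(1−p), so the observed difference is (Se + Sp − 1) times the true one. The values are again assumptions.

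| Se = Sp | Observed rates | Observed difference | False non-inferiority |
|---|---|---|---|
| 0.95 | 30.1% v 39.1% | 9.0 points | 7.9% |
| 0.90 | 32.3% v 40.3% | 8.0 points | 11.9% |
| 0.85 | 34.5% v 41.5% | 7.0 points | 17.0% |
| 0.80 | 36.7% v 42.7% | 6.0 points | 23.2% |

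Simulation with 400,000 runs agreed with the formula wherever it was run: 4.9% with no error; 8.0%, 12.1% and 17.2% at Se = Sp = 0.95, 0.90 and 0.85; 23.4% for lenient 10%; 0.1% for harsh 10%; and 47% power at equality for harsh 5%.

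**The case against.** The strongest objection is that this is a condensed article. It is silent on pathology masking and does not say that masking is absent. A full protocol exists, and the grading standards sit in a supplementary file. This objection stands in part. A reader might infer that pathology is unblinded, or that the central reader sees the local grade before verifying it, and the text supports neither inference. Verification could be a full independent re-read, and storing specimens for review fits that. It is also not stated whether the local pathologist, as distinct from the treating team, knows the arm.

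Silence does not dispose of the point, however. The article describes readers, blinding and a consensus rule for a secondary endpoint in the same section. For the primary endpoint it commits three times to local determination followed by verification. That is a stated procedure, and a better one is available.

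A second tempting inference is that knowledge of arm pushes the trial toward a false claim. It need not: the harsh rows in the table show the opposite, at the price of power. Only arm-independent error has a fixed direction, and three limits apply to it.

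- Masking alone does not remove it, because a masked reader also misgrades. The 8% to 23% range is therefore not the gain from masking.
- A central re-read of everything might already reduce it.
- The 27.9% is itself a graded rate from the phase II study. If the 10-point tolerance is meant on the graded scale, arm-independent error does not inflate the claim.

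Nor does the text support saying that the damage is beyond repair at analysis. Stored specimens would allow a masked re-read before the analysis.

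**Conclusion.** The point holds in limited form. The reading procedure for the primary endpoint is less protected, as stated, than that for a secondary endpoint, in a trial whose treating centers cannot be unaware of the arm. Arm-related grading shifts of 5% to 10% in the 2-cycle arm would matter. False non-inferiority would rise from 5% to about 12–23% if grading is lenient. If it is harsh, false non-inferiority falls to about 1% or less, but power at equality drops from 80% to about 47% or 17%. Arm-independent error over Se = Sp from 0.95 to 0.80 gives about 8–23%, subject to the limits above.

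These sizes rest on assumed error rates, since the article gives no reader-agreement figure, and on the inferred 10-point, one-sided 5% design. They show how sensitive the trial is and do not estimate a bias that has occurred. If the full protocol already specifies a masked central re-read, one sentence in the text closes the point.

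**What to change.** In the Data collection and Endpoints sections, and in the analysis plan, state that:

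1. the central review already planned grades every specimen, masked to arm, number of cycles and the local grade;
2. the central grade is the one analysed for the primary endpoint;
3. disagreements are settled by a named rule, such as the consensus approach already used for imaging;
4. the local grade is kept for agreement (kappa) and for a sensitivity analysis of the primary comparison.

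Arm and cycle number should be masked on slide labels and request forms. The cost is that masking and slightly more handling at the primary center. Central verification and specimen storage are already planned, and the sample size does not change.
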